### Design

The study is a multi-center randomized, controlled, open-label study. The participants are included during an admission with NIV treatment of AHRF due to COPD. If the patient gives consent (see below), he or she is randomized to either LTNIV or usual care. The acute NIV therapy is continued for as long the patient presents a hypercapnic acidosis or severe dyspnea without NIV; hereafter, NIV is ceased in the patients in the control group, whereas it is continued with the same settings in the LTNIV patients. When stable and when deemed appropriate by a physician, the patients are discharged.

The included patients will be given the possibility of contacting an acute hotline, operated by a nurse.

One week after discharge, all patients are visited by a nurse. The patients are followed in the outpatient departments with visits 1, 3, 6, 9, and 12 months after discharge.

A participant who is readmitted will not be re-randomized. If the participant is in the intervention group, LTNIV is resumed, if paused.

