### Consent

When stabilized and able to have a small pause from NIV, the patient is presented to the study. If interested, the patient is formally informed of the study by one of the attending physicians. This is typically 2 days after admission, although individual. The information session is held with a physician who has devoted time for this and who is not disturbed. When informed, the consent form is signed by the patient and the informing physician. If the participant wants time for consideration, a new session will be planned one or two days later.

No individual data will be published.

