### Measurements

Upon admission, we measure: arterial blood gases with *P*_a,CO2_, *P*_a,O2_, pH and *St*HCO_3_^−^, firstly to diagnose the AHRF and secondly, in order to titrate the NIV treatment; regular, venous blood samples, analyzing infectious parameters, red and white blood count, kidney- and liver parameters; electrocardiogram (ECG); and a chest x-ray.

These measurements are done as a standard at the acute admission and not as part of the protocol.

At discharge, we measure: lung function, i.e., FEV_1_, FVC and F_I_VC; peripheral oxygen saturation (*S*_pO2%_); arterial blood gases with *P*_a,CO2_, *P*_a,O2_, pH and *St*HCO_3_^−^; height and weight; MRC Dyspnea score; CAT, SRI and ESS questionnaires; and we note status of medication and long-term oxygen treatment (LTOT), when relevant.

For the intervention group, we read ventilator’s SIM card in regard to compliance, daily use, and apnea-hypopnea index (AHI).

At the home visit one week after discharge, we measure: lung function and *S*_pO2%_.

For the intervention group, we ensure that the ventilator, the mask and the hose are well-functioning; and that the patient is well informed and uses the ventilator correctly.

At the outpatient visits, we measure: lung function; *S*_pO2%_; arterial blood gases; weight; exhaled concentration of carbon mono-oxide; MRCD; CAT, SRI and ESS questionnaires; and we note status of medication, smoking, and LTOT, when relevant.

For the intervention group, we read ventilator’s SIM card in regard to compliance, daily use, and AHI.

At each outpatient visit and at the end of the patient’s study period, we collect data on mortality, hospital admissions, exacerbations treated by a general practitioner or an emergency physician, and emergency room visits.

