### Data processing

The primary outcome is the difference in time to death *or* AHRF between the LTNIV group and the control group, analyzed as an Intention-To-Treat analysis and calculated in a Cox proportional hazards regression, using Kaplan-Meier and log rank.

The differences between the study’s two groups will be computed using *X*^2^-statistics for the dichotomous variables and t-tests for the continuous variables, assuming that data will follow a normal distribution. Differences in time to a given event are calculated in a Cox proportional hazards regression, using Kaplan-Meier survival statistics and log rank.

For all comparisons, *p* < 0.05 is the level of significance.

For the sample size calculation, we used SAS (Statistical Analysis System, version 9.4).

We will use the latest versions of SAS for the statistical analyses.

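### Continuous secondary outcomes are compared by unadjusted t-tests, and almost none of them has a value taken before randomisation that could be adjusted for

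*Protocol article*

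**What the plan says.** **Analysis.** Under Data processing, differences between the arms are to be tested by chi-squared statistics for dichotomous variables and "t-tests for the continuous variables, assuming that data will follow a normal distribution". No covariate is named, and the text does not say whether final values or changes are compared. Randomisation is blocked within each of the four centres (Randomization), but centre does not appear in the analysis.

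**Order of events.** "The participants are included during an admission with NIV treatment of AHRF due to COPD" (Design). On the information session, Consent says: "This is typically 2 days after admission, although individual". The patient is then shown the allocation. When the acute episode has resolved, "hereafter, NIV is ceased in the patients in the control group, whereas it is continued with the same settings in the LTNIV patients" (Design). The next step is: "When stable and when deemed appropriate by a physician, the patients are discharged".

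**First measurements.** Measurements lists, for admission, arterial blood gases, routine blood tests, an ECG and a chest x-ray, all as standard care. The outcome measures start later: "At discharge, we measure: lung function", followed in the same list by "height and weight; MRC Dyspnea score; CAT, SRI and ESS questionnaires". They are repeated at the outpatient visits at months 1, 3, 6, 9 and 12. The apnoea/hypopnoea index is read from the ventilator, in the intervention group only.

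**The concern.** Two features of the plan combine. The two-sample t-test takes one value per patient and leaves out both the design stratum (centre) and the other visits. In addition, the value that an analyst would naturally reach for as a covariate is not a baseline. At discharge the arms have already been treated differently, and patients know their allocation when they answer CAT, SRI and ESS.

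The stake is precision for the secondary outcomes, including quality of life, which the Aim names. The second feature cannot be repaired later: an analysis plan can add a model, but it cannot supply a pre-allocation questionnaire that nobody completed. It also creates a trap. If discharge is later adopted as the baseline, part of any early treatment or expectation effect is taken out of the estimate.

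**Working it through.** **1. The plan's own figure.** The only sample-size calculation concerns the primary endpoint: risks of 63.3% and 38.5%, alpha 0.05 (taken as two-sided), power 0.80. With the unpooled two-proportion formula,

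n per arm = (1.960 + 0.842)² × (0.633 × 0.367 + 0.385 × 0.615) / (0.633 − 0.385)² = 59.9, so 60 per arm and 120 in total.

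With 20% dropout, 120 / 0.8 = 150. Both figures reproduce, and neither depends on this point. The protocol gives no SD, correlation or target difference for any continuous outcome, so the rest is in SD units and uses assumed correlations.

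**2. What a pre-randomisation covariate would be worth.** Let r be the correlation between that value and the follow-up value.

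- Variance factor: 1 − r².
- Equivalent gain in patients: 1/(1 − r²) − 1.
- Detectable difference at 80% power: (1.960 + 0.842) × √(2/n) × √(1 − r²).

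Here n is 75 per arm (all randomised) or 60 per arm (after the planned 20% dropout). The last column is power for an assumed true difference of 0.4 SD.

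| r (assumed) | Variance factor | Equivalent gain in patients | Detectable, 75 per arm | Detectable, 60 per arm | Power at 0.4 SD, 60 per arm |
|---|---|---|---|---|---|
| none (t-test) | 1.00 | 0% | 0.46 SD | 0.51 SD | 59% |
| 0.3 | 0.91 | 10% | 0.44 SD | 0.49 SD | 63% |
| 0.5 | 0.75 | 33% | 0.40 SD | 0.44 SD | 72% |
| 0.7 | 0.51 | 96% | 0.33 SD | 0.37 SD | 87% |

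**3. Why the discharge value cannot fill that role.** Suppose the arms already differ by 0.2 SD at discharge, in the same direction as a true later difference of 0.40 SD (both assumed).

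- Final values: 0.40 SD.
- Change from discharge: 0.40 − 0.20 = 0.20 SD.
- ANCOVA on discharge: 0.40 − r × 0.20 = 0.30 SD at r = 0.5 and 0.26 SD at r = 0.7.

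At 60 per arm and r = 0.5, power is 59% for the plain t-test, 48% for ANCOVA on discharge and 19% for change from discharge. In this scenario the unadjusted test does better than either analysis that uses the discharge value.

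**The case against.** The strongest reply is that the planned test is sound. Under randomisation, a two-group comparison of final values is unbiased apart from deaths and missing data. It also avoids conditioning on a post-randomisation variable, and step 3 shows that it can beat adjustment for discharge. That stands. Covariates, the visit of interest and the repeated-measures structure may also be set out in a fuller analysis plan that is not shown. That stands for the model, but not for the missing measurement.

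It is also fair that nothing in the protocol supports a correlation of 0.5 to 0.7 between a value taken about two days into an acute admission and one at month 12. At 0.3 the gain is only 9% of the variance. The time between stopping NIV in controls and discharge is not given either, so the size of any early difference is unknown.

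A reader might infer more than the text supports:

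- *That usable baseline values are recorded and simply ignored.* Apart from the admission blood gases, they are not. The protocol never calls the discharge values a baseline.
- *That the planned results would be biased.* Data processing does not specify change from discharge or adjustment for it, so this bias belongs to an analysis that the document does not propose.
- *That no continuous outcome has an earlier value.* Arterial blood gases, which the Abstract names as a secondary endpoint, are measured at admission before randomisation, although in the acute state.

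**Conclusion.** The point holds as a loss of precision in the secondary continuous outcomes, together with a gap in data collection that no later analysis can close. It does not make the t-test invalid.

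The loss is 9% to 49% of the variance for r between 0.3 and 0.7, or a detectable difference of 0.51 SD instead of 0.49 to 0.37 SD at 60 per arm. These figures rest wholly on the assumed r. They describe what would be gained if a pre-randomisation value were collected; re-analysing the data now planned would not deliver them. The attenuation in step 3 is conditional on misuse of the discharge value and on an assumed early difference of 0.2 SD.

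The change is worth making because it is cheap, but the trial's main conclusion does not depend on it.

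**What to change.** 1. **Measurements.** After consent and before the envelope is opened, record CAT, SRI, ESS, MRC dyspnoea, weight and, where feasible, spirometry. The case report file already has an admission section that could hold them.
2. **Data processing.** Replace the t-tests by a mixed model for repeated measures over months 1, 3, 6, 9 and 12 with arm-by-visit, centre and the pre-randomisation value, or by ANCOVA at month 12 with centre and that value. Name month 12 as the comparison of interest.
3. **Discharge.** Treat it as a post-randomisation time point. Do not use it as a baseline or as a covariate, including in sensitivity analyses.
4. **If no pre-randomisation value can be obtained,** compare follow-up values adjusted for centre and admission variables only.
5. **Deaths.** State how they are handled separately, because the mixed model alone treats values after death as merely missing. This matters in a population for which the Background cites a one-year mortality of 49.1%.
6. **Apnoea/hypopnoea index.** It is read only in the LTNIV arm, so no between-arm model applies; report it descriptively there.

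The cost is new analysis wording and the same instruments used a few days earlier. The downside is some burden on recently unstable patients and some missing covariate values among those who cannot complete the measures.

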### Aim

The aim of this RCT is to investigate whether LTNIV can reduce mortality or repeat AHRF in patients who have been admitted for NIV treatment of AHRF due to COPD; and, secondarily, whether LTNIV can reduce mortality per se and the number of repeat AHRF, readmissions, and exacerbations, and improve quality of life.

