### Outcomes

Primary outcome is difference in time to death *or* repeat AHRF between the study’s two groups. AHRF is defined as a pH < 7.35 and a *P*_a,CO2_ > 6 kPa despite optimal treatment according to GOLD guidelines, i.e., nebulized bronchodilators and intravenous corticosteroids [2].

The secondary outcomes are differences in the following variables; one-year mortality, admissions due to COPD; admissions due to repeat AHRF; visits to the emergency department or to an emergency physician due to COPD; exacerbations treated with oral corticosteroids or oral antibiotics; body mass index; forced expiratory volume in one second (FEV_1_); cost efficiency; health-related quality-of-life (HRQoL), measured by COPD Assessment Test (CAT) and Severe Respiratory Insufficience Questionnaire (SRI); sleep quality, measured by the Epworth Sleepiness Scale (ESS); apnea/hypopnea index (AHI); and Medical Research Council's Dyspnea scale (MRCD).

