## Discussion

This RCT will assess whether LTNIV can reduce mortality and prevent exacerbations and repeat AHRF in unstable COPD patients having survived an admission due to AHRF. Three previous RCTs have assessed LTNIV for COPD patients after an episode of AHRF, treated with NIV; the results have been conflicting as the two smaller RCTs showed that LTNIV could reduce repeat AHRF and clinical worsening [6, 7], whereas the largest RCT showed no effect [8].

In the large RCT and in one of the two small, an additional inclusion criterion was persistent hypercapnia without acidosis after the AHRF episode [7, 8].

It is documented that previous exacerbations of COPD predict new exacerbations [9] and that previous admissions due to exacerbations predict new admissions and death [10].

Based on this and on our experience with LTNIV for COPD, we believe that LTNIV can reduce mortality and repeat AHRF, regardless of whether the patient was persistently hypercapnic after the acute NIV treatment. We are looking forward to assessing this in an RCT.

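### One unadjusted 0.05 threshold covers the primary outcome and about 11 to 12 testable secondary outcomes alike, giving roughly an 18–46 % chance of a false significant secondary if none is truly affected

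*Protocol article*

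**What the plan says.** The Outcomes section names one primary: "Primary outcome is difference in time to death *or* repeat AHRF between the study’s two groups". It then opens the secondary list with "The secondary outcomes are differences in the following variables; one-year mortality, admissions due to COPD; admissions due to repeat AHRF" and continues with emergency visits, exacerbations, BMI, FEV1, cost efficiency, CAT, SRI, ESS, AHI and MRCD. Counting CAT and SRI separately, that is 13 items.

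The Aim section presents part of this list as questions for the trial: "secondarily, whether LTNIV can reduce mortality per se and the number of repeat AHRF, readmissions, and exacerbations, and improve quality of life". The Discussion says: "This RCT will assess whether LTNIV can reduce mortality and prevent exacerbations and repeat AHRF in unstable COPD patients".

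The Data processing section assigns Cox regression with log rank to time-to-event outcomes, chi-squared tests to dichotomous outcomes and t-tests to continuous ones. It then sets the decision rule for all of them: "For all comparisons, *p* < 0.05 is the level of significance".

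On timing, the Design section states: "The patients are followed in the outpatient departments with visits 1, 3, 6, 9, and 12 months after discharge". Under Measurements, lung function, weight, MRCD, CAT, SRI and ESS are recorded at these visits. AHI is read from the ventilator, in the intervention group only.

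**The concern.** The threshold sentence is a stated rule, and it draws no line between the primary and the rest. Followed literally, a null primary with one secondary at p = 0.04 would still be reported as a significant finding. Nothing in the article makes a secondary claim depend on the primary or calls the secondaries supportive.

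Three features make this more than a formality:

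- The trial is open label and several secondaries are patient-reported.
- The article describes the earlier randomized trials as conflicting, so an isolated positive secondary could be read as support for LTNIV.
- The Blinding section calls mortality the primary outcome, although mortality alone is a secondary under Outcomes. A nominally significant mortality result could easily be given more weight than the design allows.

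For the six repeatedly measured outcomes, the rule also leaves open which visit's t-test counts.

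**Working it through.** **Step 1. What the 0.05 was sized for.** Inputs from the Sample size section: risks 63.3 % and 38.5 %, α = 0.05, power 0.8, dropout 20 %. Unpooled two-proportion formula, two-sided:

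N = 2 × (1.960 + 0.842)² × [0.633 × 0.367 + 0.385 × 0.615] / (0.633 − 0.385)²
= 2 × 7.849 × 0.4691 / 0.0615 = 119.7, so 120.

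120 / (1 − 0.20) = 150. Both published figures reproduce. The calculation concerns death or repeat AHRF alone, and it matches a two-sided 0.05. The article does not state sidedness, so two-sided tests are assumed below. The article gives no family-wise error figure to reproduce.

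**Step 2. How many secondary tests there are.**

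- Listed: 13.
- Without AHI (no control-arm data described): 12.
- Also without cost efficiency (no test named): 11.
- Secondary aim only: mortality, repeat AHRF, readmissions, exacerbations, and quality of life by CAT and by SRI: 6.

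**Step 3. Chance of at least one p < 0.05 when no secondary is truly affected.** Independent tests: 1 − 0.95^k.

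- k = 6: 1 − 0.735 = 0.265
- k = 11: 1 − 0.569 = 0.431
- k = 12: 1 − 0.540 = 0.460

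For correlated tests, let the k standard normal statistics share a common correlation ρ and count |z| > 1.96:

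1 − ∫ [Φ((1.96 − √ρ·x)/√(1−ρ)) − Φ((−1.96 − √ρ·x)/√(1−ρ))]^k φ(x) dx

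| Tests | ρ = 0 | ρ = 0.5 | ρ = 0.7 | ρ = 0.8 |
|---|---|---|---|---|
| 6 (aim items) | 26 % | 21 % | 16 % | 14 % |
| 11 | 43 % | 30 % | 22 % | 18 % |
| 12 | 46 % | 32 % | 23 % | 19 % |

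Simulation with 400,000 replicates agrees (for example 0.318 for 12 tests at ρ = 0.5).

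**Step 4. Errors in favour of LTNIV only.** Counting only z > 1.96 in the favourable direction, 12 tests give 26 % at ρ = 0, 16 % at 0.5 and 9 % at 0.8.

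**Step 5. A figure that needs no correlation.** The expected number of false significant results is k × 0.05: 12 × 0.05 = 0.60, 11 × 0.05 = 0.55, and 6 × 0.05 = 0.30 for the aim items.

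**The case against.** The best defence is that this is a condensed article. Testing order, multiplicity policy and analysis visit commonly sit in the SAP or full protocol, which are not shown, so their absence alone is no defect. The article names one primary, powers the trial on it, and consistently calls the other outcomes secondary. A nominal threshold is not a promise to treat every secondary as confirmatory, and the article commits to publishing negative as well as positive results.

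Much of this stands. The absence of a hierarchy is not the point here, and the document nowhere says that a secondary can rescue a null primary. What the defence does not remove is the threshold sentence. It was written to apply to all comparisons, so an SAP that ordered the secondaries or made them exploratory would have to override it. The missing analysis visit would not be worth raising alone. It matters because the same rule would apply at whichever visit is chosen.

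Four stronger readings are tempting, and the document does not support them:

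- A reader might take 30 % as a floor. At ρ = 0.7 the figure for 12 tests is 23 %, and the six aim items never reach 30 %.
- A reader might say that no secondary has a fixed time point. Mortality is defined at one year, and both arms have a one-year follow-up over which events are collected.
- A reader might count a test at each of the five visits. The plan does not say that each visit will be tested.
- A reader might think the primary result is compromised. It is not.

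**Conclusion.** The point holds as a matter of a stated rule drawn too widely. One unadjusted 0.05 level governs the primary and about 11 to 12 testable secondaries. With no true effect on any secondary, the chance of at least one significant result is roughly 18–46 % for that set and 14–27 % for the six aim items.

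These figures assume two-sided tests, one test per outcome, every secondary null true, and a common correlation between 0.8 and 0. The article gives no correlation. Outcomes such as AHRF admissions and COPD admissions overlap, so independence is the upper extreme rather than the likely case. Errors favouring LTNIV are about half as frequent at moderate or high correlation. Even the lowest two-sided figure is well above 5 %.

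This is a worthwhile, low-cost improvement and not a threat to the trial's main conclusion.

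**What to change.** Replace the threshold sentence in Data processing with wording such as: *The two-sided 0.05 level applies to the primary outcome. All secondary outcomes are supportive or exploratory and are reported as estimates with 95 % confidence intervals, without claims of significance.* Name one analysis visit for BMI, FEV1, CAT, SRI, ESS and MRCD.

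If the sponsor wants confirmatory secondary claims, it can instead fix, before analysis, its own testing order of the secondary aims, conditional on a significant primary. The article does not supply that order in full. The Aim section says only quality of life, without choosing between CAT and SRI or naming a visit, and Aim and Outcomes list repeat AHRF and admissions in different orders. These choices are the sponsor's.

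The cost is one or two sentences before analysis, with no extra patients or data. The downside is that a secondary result could no longer be called significant when the primary is null, or when it falls outside the pre-specified order.

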### Publications

Both positive and negative results will be published in national and international journals and at conferences, symposia, etc.

### Biological material

The only biological samples taken are general blood biochemistry and arterial blood gases. This is the standard for any admission and outpatient visit. The samples are handled by the Dept. of Clinical Biochemistry according to current guidelines; after analysis, the samples are destroyed. No biological material is stored. Arterial blood gas samples measure approximately 1 mL; venous blood samples measure approximately 10–15 mL.

## Discussion

This RCT will assess whether LTNIV can reduce mortality and prevent exacerbations and repeat AHRF in unstable COPD patients having survived an admission due to AHRF. Three previous RCTs have assessed LTNIV for COPD patients after an episode of AHRF, treated with NIV; the results have been conflicting as the two smaller RCTs showed that LTNIV could reduce repeat AHRF and clinical worsening [6, 7], whereas the largest RCT showed no effect [8].

In the large RCT and in one of the two small, an additional inclusion criterion was persistent hypercapnia without acidosis after the AHRF episode [7, 8].

It is documented that previous exacerbations of COPD predict new exacerbations [9] and that previous admissions due to exacerbations predict new admissions and death [10].

Based on this and on our experience with LTNIV for COPD, we believe that LTNIV can reduce mortality and repeat AHRF, regardless of whether the patient was persistently hypercapnic after the acute NIV treatment. We are looking forward to assessing this in an RCT.

